#### Sample size calculation

A sample size of 35 in each group will be sufficient to detect a clinically important difference of 14.5 points on the FMMS, assuming a standard deviation of 21.3 FMMS points on the basis of the findings of the fluoxetine in motor recovery of patients with acute ischaemic stroke (FLAME) trial [12], using a two tailed *t*-test of the difference between means, a power of 80%, and a significance level of 5%. This number has been increased to 44 per group (total of 88), to allow for a predicted 20% loss to follow-up.

The formula for the sample size for comparison of two means (two-sided) is as follows:

$$n=\frac{2\sigma^{2}{\left(Z_{a}+Z_{b}\right)}^{2}}{\delta^{2}}$$

$$Z_{a}=1.96$$

$$Z_{b}=0.84$$

δ = size of difference of clinical importance = 14.5

σ = standard deviation of the primary outcome variable = 21.3

$$n=\frac{2*21.3^{2}{\left(1.96+0.84\right)}^{2}}{14.5^{2}}\approx 35$$

Adjusted for 20% patients lost to follow-up:

$$n_{c}=\frac{n}{1-l}\approx 44$$

*l* = expected frequency of patients lost to follow-up = 0.20

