#### Randomization method

A pharmaceutical laboratory (Psicofarma™ S.A. de C.V.) will be responsible for the manufacture and randomization of the investigational product, which will be achieved using a web-based randomization program. This program will be set to assign participants equally to each site at a ratio of 1:1.

Each of the sites will be assigned 22 participants. The manufacturer will then deliver the pre-randomized bottles containing the investigational product to each recruiting center.

Study subjects who satisfy the eligibility criteria at each recruiting center will receive the investigational product corresponding to a consecutive number assigned according to their entrance to the study.

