### Primary outcome

The primary outcome is the mean change in FMMS score between inclusion (day 0) and day 90.

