3. NIHSS

### Statistical analysis

#### Efficacy assessment

The primary and secondary outcomes will be analyzed using the intention to treat (ITT) method. The full analysis set for the ITT method will include all randomized subjects, regardless of their subsequent withdrawal after enrollment. Continuous variables will be reported as the means ± SD, and categorical variables will be reported as percentages. The Kolmogorov-Smirnoff test will be used to test normality for the continuous variables, and baseline characteristics will be compared by either Student’s *t*-test/U Mann-Whitney for continuous variables or the χ^2^ test (Fisher’s exact test when the expected value is <5) for categorical data.

The primary analysis for efficacy (full-analysis set) will consist of a comparison of the change in FMMS scores at 90 days. To handle the missing data derived from withdrawal and lost to follow-up patients, the last available outcome measure value obtained from the withdrawn/lost to follow-up patient will be used for the analysis (last observation carried forward (LOCF) strategy). A multiple linear regression analysis will be performed to control for baseline factors that show an imbalance.

For the within-group analyses, primary and secondary outcome variables will be evaluated by a paired t-test. Alternatively, for non-normally distributed data, a Wilcoxon test will be performed. Analysis of covariance will be used to analyze differences in each group, adjusting for age and NIHSS as covariates. Statistical significance will be defined as P < 0.05. SPSS for Windows version 17.0 software (SPSS, Inc, Chicago, IL, USA) will be used for the analyses.

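### The primary comparison of FMMS change prespecifies neither baseline FMMS nor site as a covariate; baseline FMMS can enter only if it happens to look imbalanced

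*Protocol article*

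**What the plan says.** All statements are in the protocol article.

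- **Primary outcome:** "The primary outcome is the mean change in FMMS score between inclusion (day 0) and day 90".
- **Primary analysis (Efficacy assessment):** "The primary analysis for efficacy (full-analysis set) will consist of a comparison of the change in FMMS scores at 90 days". No test and no covariate is named. The Sample size calculation section assumes an unadjusted two-tailed t-test.
- **Conditional adjustment, same paragraph:** "A multiple linear regression analysis will be performed to control for baseline factors that show an imbalance".
- **Named covariates, next paragraph, which opens with within-group analyses:** "Analysis of covariance will be used to analyze differences in each group, adjusting for age and NIHSS as covariates".
- **Allocation (Randomization method):** "This program will be set to assign participants equally to each site at a ratio of 1:1" and "Each of the sites will be assigned 22 participants". Pre-randomized bottles are then delivered to each centre.
- **Data available:** Table 1 schedules the FMMS at screening, Visit 2 and Visit 3. An FMMS threshold of 55 also appears among the inclusion criteria.

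**The concern.** The baseline value of the outcome is usually one of the best available predictors of its later value. A plain change-score comparison fixes the slope of day-90 on baseline at 1. Unless the true slope is 1, part of any chance baseline difference stays in the estimate and the residual variance is larger than it need be.

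The article does not leave the covariates open. It commits to age and NIHSS in one model and to a data-dependent rule in another, and neither secures baseline FMMS. The age and NIHSS model is worded as analysing differences in each group, so it is not clearly a between-arm analysis. A reader could end up with three treatment estimates (raw change, regression on imbalanced factors, ANCOVA), with no stated order between the two adjusted ones.

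Site is also left out. If allocation is balanced within site and sites differ in recovery, between-site variation stays in the error term although the design has removed it from the treatment contrast. At stake is the efficiency of an 88-patient trial planned at 80% power.

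**Working it through.** **1. The plan's own figure.** Inputs from the Sample size calculation section: difference 14.5, SD 21.3, Z values 1.96 and 0.84. Then n = 2 × 21.3² × (1.96 + 0.84)² / 14.5² = 33.8, or 34 per group. The stated 35 is what an exact t-test needs: power is 80.2% at 35 and 79.0% at 34. With 20% loss, 35/0.80 = 43.75, or 44 per group. The figures reproduce, and they rest on an unadjusted comparison. Normal-approximation power at 35 per group is 81.3%.

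**2. Gain from baseline FMMS.** Let r be the correlation of baseline with day-90 FMMS and k = (baseline SD)/(day-90 SD). The documents give neither, so both are assumed. In large samples:

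variance(ANCOVA)/variance(change score) = (1 − r²)/(1 + k² − 2rk)

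| k | r = 0.3 | r = 0.5 | r = 0.7 |
|---|---|---|---|
| 1.0 | 0.65 | 0.75 | 0.85 |
| 0.8 | 0.78 | 0.89 | 0.98 |
| 0.7 | 0.85 | 0.95 | 1.00 |
| 0.6 | 0.91 | 0.99 | 0.98 |

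For example, k = 0.8 and r = 0.3 give 0.91/1.16 = 0.78. The rows below k = 1 represent a baseline range narrowed by the FMMS threshold. The saving there is 0-22%, against 15-35% for equal SDs. As literally worded, the threshold is one of two alternative criteria, so how far it narrows the range is itself uncertain.

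In power terms, take 21.3 as the SD of change and multiply it by the square root of the ratio. At 35 per group, a ratio of 0.91 gives SD 20.3 and power 84.7%; a ratio of 0.75 gives SD 18.4 and power 90.8%; a ratio of 1.00 leaves 81.3%.

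**3. Finite-sample cost.** Estimating p slopes from N = 88 inflates the variance by about (N − 3)/(N − 3 − p). One covariate costs 85/84 = 1.012, about 1%. Three (FMMS, age, NIHSS) cost 85/82 = 1.037, about 4%, if age and NIHSS explain nothing further. At k = 0.7 and r = 0.7, where the large-sample gain is zero, adjustment therefore loses slightly.

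**4. Chance imbalance.** Assume a baseline SD of 15. The SE of the baseline difference at 44 per arm is 15 × √(2/44) = 3.2 points. The change-score estimate moves by (r/k − 1) × imbalance. For a 5-point imbalance:

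- k = 1, r = 0.5: slope 0.5, shift 2.5 points, or 17% of 14.5.
- k = 0.7, r = 0.5: slope 0.71, shift 1.4 points, or 10%.
- k = 0.7, r = 0.7: slope 1, no shift.

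Such an imbalance is 5/3.2 = 1.6 SE. If showing an imbalance means P < 0.05 on the planned baseline tests, a difference would need to reach about 1.96 × 3.2 = 6.3 points before the regression picked it up.

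**5. Site.** Assume balance within site and a site ICC, which the documents do not give. The true variance of the contrast falls by the factor (1 − ICC), while an analysis ignoring site still uses the full variance.

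| ICC | True two-sided alpha, site ignored | Power at 35/group, site ignored | Power, site fitted |
|---|---|---|---|
| 0.02 | 0.048 | 81.5% | 82.0% |
| 0.05 | 0.044 | 81.9% | 83.2% |
| 0.10 | 0.039 | 82.5% | 85.1% |

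The omission makes the test conservative, and the power lost is 0.5 to 2.6 percentage points.

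**The case against.** The strongest reply is that nothing here is invalid. Under randomization a change-score comparison is unbiased, it matches the t-test used for sizing, and it meets the 80% target at the planned SD. The gain from adjustment is of unknown size and may be negligible. Model detail for the primary comparison could also sit in an analysis plan that is not shown. The first two statements stand and limit the point to efficiency and clarity. The third carries less weight, because the article itself fixes a covariate set and an adjustment rule, and it is those choices that are questioned.

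Some stronger readings are tempting but not supported:

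- **That no baseline adjustment beyond age and NIHSS is planned.** The regression on imbalanced factors could bring in baseline FMMS. The fair criticism is that this depends on the data and can miss an imbalance that matters.
- **That the age and NIHSS ANCOVA is the primary analysis.** It stands in the paragraph on within-group analyses, and its role is unclear.
- **That randomization is documented as stratified 1:1 within site.** The ratio, the 22 per site and the bottles delivered to each centre make within-site balance the natural reading, but no strata, blocks or 11:11 split are stated.
- **That low-baseline patients must gain more.** This holds only when r/k is below 1. At k = 0.6 and r = 0.7 the slope is 1.17 and the direction reverses.

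**Conclusion.** The point holds as one of efficiency and prespecification. Neither baseline FMMS nor site is a prespecified covariate for the primary comparison, and the only route for baseline FMMS is a choice made after seeing the data.

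A reader might infer that the primary result would be biased or the false-positive rate inflated. Neither follows: across randomizations the estimate is unbiased, and omitting site can only make the test mildly conservative, with alpha about 0.039-0.048 for ICC 0.10-0.02 under within-site balance. Nor can a gain be promised in every case. The likely variance saving from baseline FMMS is 0-22% with a narrowed baseline range and 15-35% with equal SDs, before a finite-sample cost of about 1-4%. These ranges rest on assumed correlations of 0.3-0.7, assumed SD ratios and assumed ICCs, because the documents give none of them. The change is worth making because it costs almost nothing and removes an analyst's choice from the primary estimate.

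**What to change.** Name one primary model: a between-arm ANCOVA of FMMS change (or day-90 FMMS) on arm, baseline FMMS and site, reporting the adjusted difference with its 95% CI. With baseline FMMS in the model, the two outcome forms give the same treatment estimate. State that baseline FMMS is the screening value, since Table 1 schedules no FMMS at Visit 1. Age and baseline NIHSS may stay as fixed covariates if wanted.

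Let this model replace the selection of covariates by observed imbalance, and reword the age and NIHSS sentence so that it clearly describes a between-arm comparison. Use the same form for the Barthel index, modified Rankin scale and NIHSS, each with its own baseline value. Clarify in the Randomization method section whether the 1:1 ratio is enforced within each site.

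The cost is wording only, to be settled before unblinding. Every variable is already collected. The model uses 1 (intercept) + 1 (arm) + 1 (baseline) + 3 (site) = 6 parameters, or 8 with age and NIHSS, leaving 82 or 80 residual degrees of freedom from 88. The sample size need not change.

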### Adverse event reporting

Adverse events (AEs) will be recorded in medical diagnostic terminology. Detailed symptoms, duration, severity, causal relationships, actions taken, results and other information will be recorded for each AE. All AEs must be observed and recorded in the case report file (CRF) in the AE report section.

### Data quality control, data collection and data management

Data quality control will be achieved through monitoring during the trial. After checking the written CRF, well-trained clinical research associates of the principal investigator will collect the data.

### Ethical issues

This study has been approved by the institutional review boards (IRBs) at the Centenario Hospital ‘Miguel Hidalgo’, the Antiguo Hospital Civil de Guadalajara ‘Fray Antonio Alcalde’ and the Hospital Regional de Alta Especialidad ‘[name] Casassus’, and by the Bioethics Committee (reference: Oficio No. CB/304/11) and the Scientific Committee (reference: Oficio No. DIC/547/11) of the Instituto Nacional de Neurología y Neurocirugía.

Written informed consent will be obtained from each individual prior to enrollment. Research will be performed in compliance with the Helsinki Declaration and with the Good Clinical Practice Guidelines.

## Discussion

The degree of recovery and the speed of recovery from disabilities secondary to ICH are different from the recovery of patients with CI, although this difference has rarely been documented [19,20]. This is partly because the evidence comes from countries where there are a disproportionately lower number of patients with ICH compared with CI available to extract adequate conclusions. However, the existing evidence appears to demonstrate that patients with ICH recover faster and to a quantitatively greater degree compared with patients with CI. For example, in the study by Katrak et al. [21], even though the studied patients with ICH had a greater level of disability at discharge, they achieved significantly greater gains in function than patients with CI after rehabilitation. This was the case regardless of the severity of disability on admission.

The study by Nannetti et al. [22], in which 20% of the studied stroke patients suffered from ICH, patients receiving antidepressants (mostly SSRIs) made the most rapid recoveries during the hospital stay period. However, lower levels of improvement were seen after discharge, which the authors attribute to the fact that the antidepressant treatment was not continued after discharge by some patients (20.4%). This recovery was observed in the group of patients with post stroke depression (PSD) as well as in those without PSD.

The aforementioned data indicate there is a greater amount of potential motor recovery for patients with ICH compared with those with CI. Still, approximately half of ICH survivors will remain dependent on others for daily life activities [23]. The motor recovery mechanisms after stroke are still being elucidated, and most of the studies have focused on patients with CI, so little is known about the motor recovery mechanism for patients with ICH [24]. It has been demonstrated that the presence of wallerian degeneration in the pyramidal tract remote from the initial lesion on magnetic resonance (MR) images correlates with a poor outcome both in CI [25] and in ICH [26] and that the primary motor cortex (M1) plays a key role in the motor recovery of stroke patients. Strategies aimed to facilitate activity in the ipsilesional M1 or to downregulate activity in the contralesional M1 have been found to be the most useful [27]. This ipsilesional facilitation/contralesional downregulation has been attempted by modulation of somatosensory input originating in the paretic or healthy hands. Ipsilesional facilitation/contralesional downregulation is also one of the apparent mechanisms of action of selective serotonin re-uptake inhibitors (SSRIs) in the motor recovery of stroke patients, in addition to cortical reorganization and changes in the somatotopy of M1 [28].

Current guidelines recommend early supported hospital discharge and home-based rehabilitation programs as the only cost-effective intervention to aid in the recovery of ICH patients [1]. Such interventions are highly dependent on available resources and funding, which make them very difficult to implement in developing countries.

In Mexico, ICH accounts for nearly 30% of all stroke cases and produces significant functional disability and death, with 30% mortality and another 30% of patients severely disabled (modified Rankin scale >3) [29]. Up to 25% of Mexican family caregivers have to stop or cut back on work to care for stroke survivors [30]. We strongly believe that identification of a pharmacological intervention to aid in the motor recovery of patients with ICH will constitute a breakthrough that will have a major impact on the burden of disease derived from ICH in our country. We also theorize that the effect size should be bigger than that found in patients with CI.

### Trial status

The trial was first designed in 2011, and subject recruitment began in November 2012.

## Abbreviations

AE: adverse event; AHCGFAA: Antiguo Hospital Civil de Guadalajara ‘Fray Antonio Alcalde’; BCT: brain computed tomography; BI: Barthel index; CHMH: Centenario Hospital ‘Miguel Hidalgo’; CI: cerebral infarct; CRF: case report file; FLAME: fluoxetine in motor recovery of patients with acute ischaemic stroke; FMA: Fugl-Meyer assessment; FMMS: Fugl-Meyer motor scale; HAD: hospital anxiety and depression scale; HRAEJGC: Hospital Regional de Alta Especialidad ‘[name] Casassus’; ICH: intracerebral hemorrhage; ITT: intention-to-treat; INNN: Instituto Nacional de Neurología y Neurocirugía; LOCF: last observation carried forward; M1: primary motor cortex; MR: magnetic resonance; NIHSS: National Institutes of Health stroke scale; PSD: post-stroke depression; SSRIs: selective serotonin re-uptake inhibitors.
